### Baseline data collection

Baseline data collection such as basic demographics, medical history, current cardiovascular and oral anticoagulant medications, AF subtype, ablation history, HF hospitalization, and arrhythmia hospitalization history will be collected for fully enrolled subjects. Electrocardiogram patch, Holter monitor, and recent echocardiogram results obtained ≤6 months prior to implant will be collected and analyzed if data are available. The study flowchart outlining screening, enrollment, implantation, and study visits of subjects in BIO-AffectDX is shown in Figure 1.

**Figure 1 fig1:**
[figure not shown]
BIO-AffectDX Study design flowchart. AFEQT = Atrial Fibrillation Effect on Quality-of-Life Questionnaire; CRT = cardiac resynchronization therapy; IEGM = intracardiac electrogram; MLHFQ = Minnesota Living with Heart Failure Questionnaire; NYHA = New York Heart Association classification; PGA = Patient Global Assessment; VT = ventricular tachycardia.

### Device implantation

Patients will be implanted with a CRT-DX system according to current clinical standards, based on current guideline-based clinical indications for a CRT-D. Implantation with a CRT-DX system can take place no more than 30 days after consent. The CRT-DX system will be determined by the site investigator to be a successful implantation of the CRT-DX pulse generator, a DX ICD lead, and a quadripolar LV lead. A CRT-DX system is considered “unsuccessful” if any component of the CRT-DX system (CRT-DX pulse generator, DX ICD lead, and LV lead) is attempted to be implanted but could not be placed in a stable position, or if the CRT-DX system is unable to deliver adequate therapy owing to any cause attributable to the implant procedure as determined by the investigator. Additionally, geographic location of the atrial dipole within the atrium will be assessed visually by the site investigators. The anatomic locations within the atrium will be characterized at the time of implant as upper third, mid third, lower third, or unknown. Lead implantation and implant approaches will be performed according to institutional standard procedures of the enrolling centers. Although it is not required by protocol, sites choosing to perform defibrillation threshold testing will do so according to their institutional standards.

### Device programming

In the BIO-AffectDX study the devices are programmed to achieve maximal biventricular pacing percentage; therefore, at a minimum, LV pacing is required to be programmed ON. The pulse generators in this study provide a wide range of mode settings and 20 different LV pacing vectors and configurations, including integrated bipolar LV pacing and true LV bipolar pacing. Additional programming options that are available include triggered pacing and timing options such as initially paced chamber and/or interventricular delay programming. The protocol allows for investigator judgment in determining these features for individual subjects. The percentage of CRT pacing will be determined and confirmed by analyzing device diagnostics from in-office interrogations and home monitoring transmissions. DX sensing, home monitoring transmission to allow collection and evaluation of daily remote data, and intracardiac electrogram collection for tachycardia therapy are to be programmed ON. Study subjects should be registered in the Home Monitoring Service Center as soon as possible following implant. Specific bradyarrhythmia settings, tachyarrhythmia settings, and CRT optimization are at the discretion of the investigator. Required and recommended settings for programmed parameters are provided in Table 2.

**Table 2 tbl2:** Required and recommended programmed parameters

Parameters	Programmed setting
Ventricular pacing	BiV (required)
DX sensing	ON (required)
BIOTRONIK Home Monitoring®	ON (required)
IEGMs for therapy episodes	ON (required)
SMART Detection®	ON
ICD therapy	ON
MPP	OFF

ICD = implantable cardioverter-defibrillator; IEGM = intracardiac electrogram; MPP = multipole pacing.

### Follow-up

Following patient consent and the implantation procedure, subjects will be evaluated during in-office follow-up visits at 3, 6, and 12-month postimplant. Subject assessments at each visit will include an Atrial Fibrillation Effect on Quality of Life questionnaire, Minnesota Living with Heart Failure Questionnaire, and an NYHA class assessment. In addition, a Patient Global Assessment (PGA) will be given to collect the patient’s reported rating of overall health at each follow-up compared to prior to receiving the CRT system. Subject responses to the PGA are captured on a scale of 7 responses, from Markedly Better to Markedly Worse. Additionally, at the 6- and 12-month visits a 6-minute walk test will be administered. After completion of subject assessments, a routine device interrogation, review of all stored device-classified VT and VF shock intracardiac electrograms, and cardiovascular and oral anticoagulation medication reconciliation will occur. An evaluation of current atrial rhythm via a standard method (3-lead, 5-lead, 12-lead, programmer strip, etc) will also be collected. Echocardiography data will be obtained and analyzed for subjects with routine echocardiography testing data available both at baseline and 12-month follow-up. Some of the echocardiography data of interest will include left atrial size and LV dimensions and degree of mitral regurgitation in addition to other clinically relevant parameters. Adverse events including HF, arrhythmia, and death events will be collected at each visit.

Telehealth follow-up visits are replacing in-office follow-up visits in many centers. While the BIO-AffectDX Study strongly recommends an in-office visit whenever possible, telehealth visits in conjunction with a live phone or video call between the subject and investigational site staff are allowed. As conventional methods used to obtain a subject’s cardiac rhythm status are not available during a telehealth follow-up visit, an on-demand remote device data download will be used to provide current rhythm status for the subject.

### Ablation/cardioversion procedures

Ablation and cardioversion procedures occurring during the study will be documented. Specifically, atrial rhythm pre- and postprocedure, date and type of procedure, success of procedure, postprocedure device programming and settings, and any reportable adverse events will be obtained. Success of these procedures will be determined and specified by the site investigator based upon their clinical experience. Additionally, cardioversion from AF identified by site personnel to be the result of shocks delivered during the implantation procedure will be captured.

### Data analysis

For all study objectives and any additional data of interest collected, descriptive statistics will be used to present and summarize the data collected during the study.

Frequency distributions and cross-tabulations will be presented for discrete variables. Means, standard errors, and ranges will be presented for continuous variables.

The primary objective of this study is to evaluate the number and percentage of all HF patients with paroxysmal, persistent, and long-standing persistent AF subtypes showing improvement from baseline at 12 months. A CCS based on changes in NYHA class, PGA status, HF hospitalization status, and all-cause death is utilized to define the primary objective. The primary objective will be assessed by performing an exact point estimate and 1-sided upper 95% confidence interval for the rate of improvement.

The CCS employs a hierarchical method to classify each subject with a status of “Improved,” “Worsened,” or “Unchanged.” A patient is classified as “Worsened” if they have experienced death due to any cause, a HF hospitalization, a moderate or marked worsening in PGA, or worsening of NYHA functional class compared to baseline. A patient is considered “Improved” if they improved in at least 1 of the NYHA or PGA and did not worsen in any component. All other patients are classified as “Unchanged.” The hierarchy to determine CCS classification is displayed in Figure 2. The PGA will ask subjects to assess how their overall status has changed since prior to receiving CRT therapy.^27^^,^^28^

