## Objectives

The primary objective of this study is to evaluate the percentage of all HF subjects with an improvement in a clinical composite score (CCS) from pre-CRT implant to 12 months. Subjects will be stratified by paroxysmal, persistent, and long-standing persistent AF subtypes implanted with a 2-lead CRT-DX system.

Secondary objectives include the following: (1) to evaluate the rate of composite all-cause death and HF hospitalizations through 12 months; (2) to compare AF subtypes for CCS status, changes in Atrial Fibrillation Effect on Quality-of-Life Questionnaire, changes in Minnesota Living with Heart Failure Questionnaire, changes in NYHA, changes in 6-minute walk test, and changes in AF burden at 6 and 12 months; (3) to evaluate the proportion of subjects showing improvement from pre-CRT using a CCS at 6 months; (4) to evaluate the observed major complication rates from device implantation in this population at 12 months; (5) to evaluate the percentage of subjects converting to sinus rhythm at any time during the 12-month follow-up period, along with reason for conversion, both overall and by AF subtype.

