
### Sample size justification

There is no formal inferential analysis scheduled for the primary objective. The study was designed to limit the number of subjects involved, while still providing CRT-DX therapy to a sufficiently large subject population to ensure a representative and statistically meaningful sample. It is anticipated that at least 400 subjects will be implanted and followed through 12 months postimplantation at up to 50 US sites. The sample size required to assess the primary objective is based on the precision of improvement from baseline achieved using an exact point estimate and 1-sided upper 95% confidence interval. The sample size for the primary objective was calculated based on the following assumptions:

The standard normal approximation to the 95% confidence interval associated with an estimate of a binomial parameter (p) is given by:

95% Confidence Interval: p ± 1.96 [ p (1 − p) / n ]^1/2^

To meet the enrollment goals for the BIO-AffectDX study, target enrollment percentages within each AF subtype and based on prior use of CRT-DX systems are defined as 50%, 30%, and 20% of the total study population for paroxysmal, persistent, and long-standing persistent AF, respectively. Therefore, it is expected that no single AF subtype will be greater than 60% of the total study population.

A limitation of using the above method is that secondary and subanalyses are exploratory and will not be adequately powered. This will be mentioned in all results, with confidence intervals and effect sizes also given to provide complete transparency, with a clear distinction that owing to small samples, the results likely overestimate the true effect size in the population.

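### The primary improvement rate is given only a one-sided upper 95% limit, which does not bound how low the rate could be, and the sample size section pairs it with a two-sided formula

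*Protocol article*

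**What the plan says.** The Objectives section sets the primary aim as to "evaluate the percentage of all HF subjects with an improvement in a clinical composite score (CCS) from pre-CRT implant to 12 months". A higher percentage is the better result.

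The Data analysis section fixes how that percentage is reported: "The primary objective will be assessed by performing an exact point estimate and 1-sided upper 95% confidence interval for the rate of improvement".

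The Sample size justification section uses the same interval as the basis for the number of subjects, namely the "precision of improvement from baseline achieved using an exact point estimate and 1-sided upper 95% confidence interval". It then introduces a formula with the words "The standard normal approximation to the 95% confidence interval associated with an estimate of a binomial parameter (p) is given by" and prints "95% Confidence Interval: p ± 1.96" times the standard error. It also says: "There is no formal inferential analysis scheduled for the primary objective".

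The last paragraph of Data analysis promises 95% confidence intervals for the subanalyses. The article states no other interval for the primary rate.

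**The concern.** There are two problems, both in the wording of the primary analysis.

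**Direction.** An upper limit answers the question of how high a rate could be, which suits a complication rate. For a rate of improvement the reader wants to know how low the true value could be. A one-sided upper interval for a proportion runs from 0 to the limit, so every poor rate stays inside it.

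**Sidedness.** The sample size section describes a one-sided interval and prints a two-sided one. The precision that the formula yields is not the precision of the interval that will be reported.

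With no formal test planned, this interval is the only stated measure of uncertainty for the primary result. The article also says that outcomes may be compared with published rates or with a sinus-rhythm CRT-D group. An upper limit alone could show that the rate lies below a comparator. It could not show that the rate lies above one, or is no worse by some margin.

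**Working it through.** **Inputs**
- Number of subjects: 400 (Sample size justification).
- Planned interval: exact, one-sided, upper, 95% (Data analysis and Sample size justification).
- Printed formula: p ± 1.96 × √[p(1 − p)/n] (Sample size justification).
- Expected improvement rate and target half-width: not given in the text shown. Observed rates of 50%, 60% and 70% are assumed below to show a range.

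**Step 1: the plan's own figure.** The 400 cannot be reproduced uniquely, because neither the expected rate nor the target precision is shown. The printed formula at n = 400 gives:
- p = 0.5: 1.96 × √(0.25/400) = 4.9 points
- p = 0.6: 1.96 × √(0.24/400) = 4.8 points
- p = 0.7: 1.96 × √(0.21/400) = 4.5 points

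For a half-width of 5 points at p = 0.5 the formula needs 1.96² × 0.25 / 0.05² = 384.2, so 385 subjects. That is close to 400 but does not equal it.

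**Step 2: sidedness.** A one-sided 95% limit uses 1.645. The distance from estimate to limit becomes 4.1, 4.0 and 3.8 points at the same three rates. The ratio 1.645/1.96 = 0.84, so the one-sided distance is about 16% shorter. The 5-point target at p = 0.5 would then need 1.645² × 0.25 / 0.05² = 270.6, so 271 subjects.

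**Step 3: exact limits at n = 400.** For x improved out of n, the Clopper-Pearson upper limit is the 1 − a quantile of Beta(x + 1, n − x), and the lower limit is the a quantile of Beta(x, n − x + 1). Here a = 0.05 for a one-sided limit and 0.025 for each side of a two-sided interval.

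| Improved (assumed) | Planned one-sided upper interval | Two-sided 95% interval | One-sided lower limit |
|---|---|---|---|
| 200 (50%) | 0 to 54.2% | 45.0 to 55.0% | 45.8% |
| 240 (60%) | 0 to 64.1% | 55.0 to 64.8% | 55.8% |
| 280 (70%) | 0 to 73.8% | 65.2 to 74.5% | 66.0% |

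The planned interval always starts at 0, whatever is observed.

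**Step 4: effect on the sample size.** At n = 400 the two-sided exact interval lies about 5 points either side of 50%. The 1.96 formula is the more demanding of the two, so moving to a two-sided interval needs no more subjects.

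**The case against.** The strongest reply is that nothing is decided on this limit. The article schedules no formal inference for the primary objective, sets no performance goal and calls its results hypothesis generating. That stands, and it limits the weight of the point. No type I error or power is involved.

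A second reply is that the number and percentage improved will be reported, so anyone can compute a lower limit. That also stands. A reader might infer that the study cannot tell how low the rate is. The documents do not support that: the data carry the information, and only the planned report omits it.

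A reader might also infer that the analysis defeats a claim that at least some given percentage improve. The article states no such claim; its objective is to evaluate the percentage.

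A third reply is that upper may loosely mean an interval running upward from a lower limit. The full protocol might settle this. As printed, in two sections, the words describe an upper limit. If the loose reading were right, the direction point would fall away, but the 1.96 would still not match a one-sided 95% limit.

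Finally, a reader might object to planning with a normal approximation and analysing with an exact method. That is ordinary practice. At 400 subjects and 60% it compares ±4.8 points with 55.0 to 64.8%, a trivial difference, and is no fault here.

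**Conclusion.** The point holds as a moderate correction to how the primary result is reported. As written, the only planned interval for a benefit rate has no informative lower end, and the sample size section pairs a one-sided interval with a two-sided formula.

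The difference for the reader is that between 0 to 64.1% and 55.0 to 64.8% at an assumed 60%, with the same pattern at 50% and 70%. These figures assume that all 400 subjects contribute to the analysis; the rates are illustrations, since the article gives none.

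A reader might take the sidedness mismatch to mean that 400 is too few. It does not, because the formula used is the more conservative one. Nor is the absence of an expected rate or target precision counted as an error, since these may stand in the full protocol.

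**What to change.** In Data analysis and in Sample size justification, replace the one-sided upper interval with an exact (Clopper-Pearson) two-sided 95% confidence interval for the rate of improvement. If a one-sided statement is preferred, specify the lower 95% limit instead.

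In Sample size justification, state the planned precision for whichever interval is chosen, with a multiplier that matches its sidedness. For the two-sided exact interval this is about ±5 points at 400 subjects and a rate of 50%.

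The cost is a sentence or so in each of the two sections. No extra subjects, visits or data are needed. The change should be made before results are known, so that the interval is not chosen afterwards.

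### The clinical composite score sets a PGA grade for Worsened but none for Improved, so read literally a slightly better PGA alone can count toward the primary rate

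*Protocol article*

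**What the plan says.** The CCS is defined in the protocol article under Data analysis. Death from any cause or a heart failure hospitalization makes a subject Worsened, and so does "a moderate or marked worsening in PGA, or worsening of NYHA functional class compared to baseline". A subject is Improved "if they improved in at least 1 of the NYHA or PGA and did not worsen in any component". Everyone else is Unchanged. The section then points to a diagram: "The hierarchy to determine CCS classification is displayed in Figure 2".

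Under Follow-up, the PGA is "captured on a scale of 7 responses, from Markedly Better to Markedly Worse", and the patient compares current health with health before the CRT system.

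The primary objective is the proportion Improved at 12 months, assessed by "performing an exact point estimate and 1-sided upper 95% confidence interval for the rate of improvement". Under Objectives, the same score is used for the 6-month improvement rate and for comparing AF subtypes at 6 and 12 months. Under Sample size justification: "There is no formal inferential analysis scheduled for the primary objective".

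**The concern.** Two neighbouring sentences treat the PGA differently. The first gives a grade (moderate or marked) before PGA worsening counts. The next gives none before PGA improvement counts. With seven responses there is room for a lesser grade on each side, so the ordinary reading is that any better answer is enough.

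The smallest positive answer then decides the class of some subjects. In an uncontrolled study whose patients know they have the device and rate themselves against their own past, that answer is plausibly the one most exposed to expectation and recall, and no control arm offsets this. If the threshold is settled only when the derived variable is programmed, the choice could also be made after the data are seen.

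A smaller ambiguity sits in the same sentence. The condition of no worsening in any component does not say whether a slightly worse PGA, which does not meet the Worsened criteria, still bars Improved.

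**Working it through.** **Inputs from the article.** The CCS rule (Data analysis); a PGA with seven responses (Follow-up); n = 400 and the formula p ± 1.96·√[p(1−p)/n] (Sample size justification). The article states no expected improvement rate and no target precision, so there is no planned figure to reproduce.

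**Assumption.** Only the end labels of the PGA are given. I take three better grades (slight, moderate, marked), no change, and three worse grades.

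**Step 1: enumerate the rule.** Among subjects without death or heart failure hospitalization there are 3 NYHA outcomes × 7 PGA answers = 21 cells. Read literally:

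| NYHA | PGA moderately/markedly worse | slightly worse | no change | slightly better | moderately/markedly better |
|---|---|---|---|---|---|
| worse | Worsened | Worsened | Worsened | Worsened | Worsened |
| same | Worsened | Unchanged | Unchanged | **Improved** | Improved |
| better | Worsened | Improved or Unchanged* | Improved | Improved | Improved |

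*Depends on whether slight PGA worsening bars Improved.

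**Step 2: match the thresholds.** Require at least moderate PGA improvement and hold the treatment of the starred cell fixed. One of the 21 cells changes: NYHA same with PGA slightly better moves from Improved to Unchanged. This is so under either reading of the starred cell. If s is the share of all subjects in that cell,

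rate (matched) = rate (literal) − s.

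The literal rate can therefore only be equal or higher.

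**Step 3: does the Worsened threshold itself matter?** Counting any PGA worsening as Worsened would move NYHA same with PGA slightly worse from Unchanged to Worsened, which leaves the Improved count alone. It would remove subjects from Improved only in the starred cell, and only if slight worsening does not already bar Improved. What raises the rate is the missing grade for improvement, not the grade set for worsening.

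**Step 4: compare with sampling precision at n = 400.**
- p = 0.5: 1.96 × √(0.25/400) = 4.9 points
- p = 0.6: 1.96 × √(0.24/400) = 4.8 points

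With the one-sided multiplier 1.645 these become 4.1 and 4.0 points.

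**Step 5: put in assumed values of s.** Starting from a literal rate of 60%, itself an illustration:

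| s (assumed) | subjects of 400 | matched rate |
|---|---|---|
| 5% | 20 | 55% |
| 10% | 40 | 50% |
| 20% | 80 | 40% |

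At s = 5% the shift already slightly exceeds the 4.8-point half-width.

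**The case against.** The strongest reply is that the words *any improvement* appear nowhere. The text is silent on the grade and refers the reader to Figure 2, which could not be seen here. A condensed article may leave the grade to that figure. This stands as a limit: the figure may already set the threshold. It does not remove the point, because the text gives a grade on one side only and should agree with the figure.

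On the second ambiguity, it can be said that worsening in any component naturally refers back to the criteria just listed. That is the likelier reading, and one clause would settle it.

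A reader might infer that a population with no real change would be scored mostly as improved rather than worsened. The rule does not support this. Worsened has four routes (death, hospitalization, PGA, NYHA), all overriding, and Improved has two. As an illustration, take seven equally likely PGA answers, independent NYHA change, and slight worsening not barring Improved:
- NYHA 20% worse and 20% better, no events: Worsened 1 − 0.8 × 5/7 = 42.9%; Improved 0.6 × 3/7 + 0.2 × 5/7 = 40.0%.
- NYHA 10% and 10%, no events: Worsened 1 − 0.9 × 5/7 = 35.7%; Improved 0.8 × 3/7 + 0.1 × 5/7 = 41.4%.
- The same with 15% having an event: Worsened 0.15 + 0.85 × 35.7% = 45.4%; Improved 0.85 × 41.4% = 35.2%.

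The balance depends on the inputs.

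A reader might also infer that comparability with published rates is lost. The article says only that such comparisons may be made, and the thresholds used elsewhere cannot be known from it.

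Finally, the 5-20% share is an assumption, so the comparison with the half-width shows what could happen and does not estimate what will.

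**Conclusion.** The point holds in a limited form. As worded, the rule is asymmetric in the PGA. Under the literal reading the direction is certain for a fixed treatment of the starred cell: the improvement rate is equal to or higher than under a matched threshold, point for point with the share whose only improvement is a slightly better PGA. The size cannot be derived from the article.

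It should be corrected before analysis because it bears on the primary result and on the 6-month and subtype CCS results. It is not a critical flaw. With no hypothesis test, no performance goal and results declared hypothesis generating, no error rate or pass/fail decision depends on it. What suffers is the meaning and reproducibility of the reported rate. The conclusion rests on the assumed PGA labels and on Figure 2 not already supplying the grade.

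**What to change.** Define Improved as NYHA class improved and/or PGA moderately or markedly better, with no component meeting the stated Worsened criteria. Say that a slight PGA change in either direction is neutral, which also settles the second ambiguity. Make the text and Figure 2 agree, apply the same rule at 6 and 12 months, and report the rate under any PGA improvement as a sensitivity analysis.

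The cost is a sentence or two and one derived variable, since all seven responses are already collected. The downside is a possibly less favourable rate. The net change is not always −s: if slight PGA worsening was meant to bar Improved, making it neutral adds back the share with better NYHA and slightly worse PGA. The sensitivity analysis should therefore vary the improvement grade alone, so that its effect can be read off.
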